#### Secondary outcomes

Child Behaviour Checklist Externalising Scale (CBCL: [34]). The Externalising scale comprises syndrome scores for behaviours related to attention and aggression.

Parent-Child Early Relational Assessment (PCERA: [49]), a clinician-rated measure, is based on observations of mother-child behaviours that provides an independent rating of infant behaviour. Videos of a structured task and free play are coded by a trained, blinded observer. All subscale scores demonstrated high levels of internal consistency, with coefficients ranging from 0.75 to 0.96. The following eight items measuring child depressed affect, anxiety, hyperactivity, and self-regulation are used in this study: Apathetic/Withdrawn/Depressed Mood, Sober/Serious Mood, Anxious/Tense/Fearful Mood, Attentional abilities, Hyperactivity, Persistence, Impulsivity, and Self-regulation.

Revised Infant Behaviour Questionnaire (IBQ-R: [50]). The IBQ-R includes fourteen sub-scales: approach, vocal reactivity, high intensity pleasure, smiling and laughter, activity level, perceptual sensitivity, sadness, distress to limitations, fear, falling reactivity/rate of recovery from distress, low intensity pleasure, cuddliness, duration of orienting, and soothability. The sub-scales have adequate internal consistency (alpha = 0.71 to 0.90) and positive inter-rater agreement.

Ages & Stages Questionnaires (ASQ-3, ASQ-SE: [32], [33]). The ASQ provides an early, parent-reported evaluation of developmental progress. ASQ-3 sub-scales have good to acceptable internal consistency (alpha = 0.51 to 0.87), strong test-retest reliability (r = .75 to 0.82), and robust inter-rater reliability (r = .43 to 0.69). ASQ-SE sub-scales have adequate internal consistency (Cronbach’s alpha ranged from 0.67 to 0.91). ASQ-SE has test-retest reliability of 94%. Based on the results of our pilot study we chose to focus in this study on the problem solving domain of the ASQ-3 and the communication and self-regulation domains of the ASQ-SE at the 3- and 12-month postnatal time point. At the 24-month time point participants are asked to complete the communication, gross motor, fine motor, and problem solving ASQ-3 domains.

### Maternal measures

Structured Clinical Interview for DSM-5 – Clinician Version (SCID-5-CV: [44]). Diagnosis of current depressive disorder as an inclusion criterion is determined by a blinded psychologist via this gold-standard psychiatric interview conducted over the telephone. This interview is also used to determine other diagnoses or symptoms set as exclusion criteria (i.e., psychotic symptoms, bipolar disorder and substance use disorder). The tool has excellent inter-rater and test-retest reliability (kappa > 0.70) [51].

Beck Depression Inventory Revised (BDI-II: [52]) is a widely used, well-validated, 21-item clinical measure of severity of depression. The BDI-II has been validated against gold-standard diagnostic criteria in perinatal populations [53].

Beck Anxiety Inventory (BAI: [54]) is a 21-item measure of anxiety with well-established properties, including in perinatal populations [53].

Perceived Stress Scale (PSS: [55]) is the most widely used psychological instrument for measuring the perception of stress. This scale has acceptable internal consistency (alpha > 0.70) and test-retest reliability (r > .70) [56].

Parenting Stress Index (PSI: [57]) is a validated and well-researched 101-item parent report measure of parent-child relationship functioning and attachment.

Demographic and descriptive data. Data are collected on sample demographics (socio-economic indicators and pregnancy information; e.g., prenatal care, smoking, alcohol use, sleep patterns, history of depression during pregnancy), obstetric and birth information (e.g., birth weight, gestation, major complications), psychosocial factors (e.g., history of mental illness) and resource use (other services/medication accessed between follow-ups). Data on the impact of COVID-19 on maternal mental health, child behavioural development and related issues have been collected between January 2021 and February 2023.

### Safety monitoring

Maternal mood is monitored through questionnaires at four follow-up time points and also through the SCID at two of these time points. When risk of self-harm is indicated in the BDI-II [54] by either a positive score on item 9 and/or overall score within the severe range, or during the SCID, a risk assessment is completed. Participants deemed to be at low-to-moderate risk are referred to their GP and are provided with information on other available supports. Participants deemed to be at high risk are referred to receive immediate crisis attention [45].

### Data management

All participants are allocated a confidential trial code. The master coding database is kept in a secure computer drive with access restricted to the lead investigators, trial co-ordinator, and treating psychologist. All de-identified data are entered in a secure computer drive. Data entry is performed by the trial co-ordinator and data checks are performed regularly by the lead investigators. De-identified paper files are stored in locked filing cabinets, accessible only to the research team. Audio recordings of interviews and video recordings of parent-infant interaction are de-identified and are saved in secure computer drives only accessible to the research team. Only collated group data will be presented or published.

### Statistical methods

#### Power & Sample size calculations

The study is powered with respect to the primary outcome, the Internalising scale of the CBCL at 24 months. In our pilot data the control group standard deviation (SD) for the Internalising scale was 6.6. For the Internalising scale at 24 months, a between-group (treated vs. non-treated) mean difference of 3.3 points is considered the MCID as it equates to ½ SD difference [58, 59]. With SD = 6.6, the required n to detect a mean difference of 3.3 points in the Internalising scale with 80% power at alpha (two-tailed) = 0.05 is 15.7*(6.6/3.3)*2 = 63 per group. We typically see less than 20% loss to follow-up in our larger perinatal RCTs [48, 60]. For caution, we are allowing for a prudent margin of 25% attrition. This yields n* = 63/(1–0.25)2 = 112 which rounds to 115 per group (n = 230 in total).

A sensitivity analysis in G*Power confirms that with n = 230, both moderate and large effects have high reliability of being detected (power > 90%) and small effects will be reliably detected with power = 70%; even in models including up to six covariates. Thus, the study is sufficiently powered to detect the MCID in the primary child outcome (Internalising scale at 24 months).

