### Our CBT intervention for antenatal depression and its effect on child development

Our antenatal CBT treatment for depression, Beating the Blues Before Birth, has been trialled and validated for its effect on child development in a pilot study [22]. In a feasibility study, the treatment has proved to be highly effective at reducing both depression and associated anxiety in a population of pregnant women diagnosed with depression (80% with major depressive disorder) [22]. The pilot RCT that followed is to our knowledge one of only a very few published trials reporting the impact of antenatal depression treatment on child behavioural outcomes [22]. In this pilot RCT (n = 54), substantial reductions were achieved in maternal depression and anxiety in the intervention group compared to TAU. Depression gains were maintained at 9 months postpartum (Cohen’s d = 0.67, p = .05). The intervention group showed excellent treatment adherence. Of a possible eight sessions, women in the intervention attended an average of 6.30 (SD 2.91); 78% attended six or more sessions, and 63% completed all eight sessions. At 9 months, the largest effects [29] on child outcomes were seen on the Infant Behaviour Questionnaire-Revised (IBQ-R: [30]) including subscales measuring negative affectivity (d = 0.84, p = .03) and stress reactivity (d = 1.08, p = .007). Stress reactivity in infants is a specific area that is impacted negatively by maternal mental health difficulties in pregnancy [31]. Several subscales of the Ages & Stages Questionnaire-3 and Ages & Stages Questionnaire Socio-Emotional (ASQ-3 and ASQ-SE: [32], [33]) also showed large effects favouring the intervention group children at 9 months including self-regulation (d = 0.83, p = .03) and communication (d = 0.81, p = .04). Our follow-up study in this cohort demonstrated differences in child behaviour at 24 months [23]. On the CBCL [34], medium-to-large effect sizes [29] were seen in behaviours comprising the Internalising scale, especially ‘withdrawal’ and ‘anxious/depressed’ behaviours (d = 0.57 and 0.59 respectively) and in emotional self-regulation (d = 0.42). Intervention group children also trended towards lower scores (d = 0.5) on the DSM-oriented Anxiety Problems scale (which maps CBCL items to DSM anxiety diagnoses). Furthermore, five out of seven syndrome subscales showed a trend in favour of the intervention group. Motor and cognitive development (assessed with the Bayley Scales: [35]) showed small-to-medium sized effects in the same direction (d = 0.52 and d = 0.26 respectively). While highly encouraging, our pilot work was based on a relatively small sample and the current protocol describes a fully-powered study capable of reliable statistical detection of a MCID in early child behavioural problems. To our knowledge this is the first adequately-powered study with medium-term follow-up to determine whether effectively treating maternal depression exclusively in pregnancy has a beneficial effect on child outcomes.

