### Study design

This is a multi-centre, parallel, two-group RCT designed to recruit 230 depressed pregnant women with a 1:1 allocation ratio to either CBT or TAU (n = 115 in each condition) within a superiority framework. The design is shown in Fig. 1. This protocol follows the recommendations of Standard Protocol Items: Recommendations for Interventional Trials (SPIRIT: [38]), Guidelines for Reporting Trial Protocols and Completed Trials Modified Due to the COVID-19 Pandemic and Other Extenuating Circumstances (CONSERVE-SPIRIT extension: [39]), and Template for Intervention Description and Replication (TIDieR: [40]). The research is being conducted in line with Consolidated Standards of Reporting Trials (CONSORT) standards [41] and the National Statement on Ethical Conduct in Research Involving Humans.

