### Trial status and summary

This is an Australian-based randomised trial comparing the emotional and behavioural development of children whose mothers received an 8-week psychological treatment for antenatal depression to children whose mothers received treatment as usual. The protocol has been amended three times as detailed below and the current protocol version is 4 dated 5 August 2021. The trial was registered and approved on the Australian and New Zealand Clinical Trials Registry prospectively in 27 November 2018 and last updated 1 July 2022. Recruitment commenced at site 1 on 29 November 2018, at site 2 on 10 June 2020, at site 3 on 13 September 2021 and at site 4 on 2 November 2022. At the time of manuscript submission, 707 have been referred (self-referred 673, through hospitals 34) to the study, 177 have had a clinical assessment and 102 participants had been randomised to the trial (CBT n = 51; TAU n = 51).

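### The allowance for 25% attrition divides by (1 − 0.25) squared, so 230 is not the size that follows from 80% power at 25% loss; it gives about 90% power (a conservative error)

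*Protocol article*

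**What the plan says.** All of the inputs are in the Protocol article, under Power & Sample size calculations.

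- Variability: "In our pilot data the control group standard deviation (SD) for the Internalising scale was 6.6".
- Target difference: a "mean difference of 3.3 points is considered the MCID as it equates to ½ SD difference".
- Error rates: "with 80% power at alpha (two-tailed) = 0.05".
- Number needed with complete outcomes: "15.7*(6.6/3.3)*2 = 63 per group".
- Attrition: the authors report that fewer than 20% are usually lost in their larger perinatal trials, and they set the allowance at 25% for caution.
- Inflation: "This yields n* = 63/(1–0.25)2 = 112 which rounds to 115 per group (n = 230 in total".

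The Study design section carries the result forward: the trial is "designed to recruit 230 depressed pregnant women with a 1:1 allocation ratio". A further paragraph of the sample-size section reports a G*Power check at n = 230, with power above 90% for moderate and large effects. That check is not tied to any level of attrition.

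The Statistical analyses section treats lost outcomes as missing data. The primary analysis is by intention-to-treat, run once on observed data and once with multiple imputation.

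**The concern.** Two different problems call for two different inflation factors. If a fraction L of participants have no outcome, the analysed number falls to (1 − L) of those randomised, and one divides by (1 − L). If a fraction L lose the treatment effect but are still measured and analysed as randomised, the mean difference shrinks by (1 − L). Sample size depends on the inverse square of the difference, so one then divides by (1 − L)².

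The article names only the first problem and applies the factor for the second. As written, the chain from 80% power and 25% attrition to 230 women does not hold.

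At stake is an accurate account of what the target buys. Recruitment has been slow: at submission, "102 participants had been randomised to the trial (CBT n = 51; TAU n = 51". The CONSERVE-SPIRIT statement records longer recruitment time frames and extra funding. Anyone judging how much a shortfall from 230 would cost in power cannot get a correct answer from the printed formula.

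**Working it through.** **1. Reproduce the plan's 63.** With σ = 6.6, δ = 3.3, two-sided alpha 0.05 and 80% power:

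n = 2(1.96 + 0.8416)² × (σ/δ)² = 15.70 × 2² = 62.8, so 63 per group. The t-test version is 63.8, so 64. The printed multiplier of 2 and a square give the same answer here because 6.6/3.3 = 2. The plan's figure is confirmed.

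**2. Find which divisor gives 112.** The superscript may have been lost in print, so each reading was tried:

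| Reading | Result per group |
|---|---|
| 63/(1 − 0.25) | 84 |
| 63 × 1.25 | 78.75, so 79 |
| 63/((1 − 0.25) × 2) | 42 |
| 63/(1 − 0.25)² | 112.0 |

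Only the squared divisor reproduces 112. The square was applied in the calculation, so this is more than a typesetting matter.

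**3. Inflate for missing outcomes only.** 63/0.75 = 84 per group, 168 in total. From the t-test figure, 64/0.75 = 85.3, so 86 per group, 172 in total. The planned 230 is 58 to 62 women more.

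**4. What 115 per group delivers.** With m analysed per group, power ≈ Φ[(δ/σ)√(m/2) − 1.96].

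- No loss, m = 115: Φ(3.791 − 1.96) = 96.6% (t-test 96.5%).
- 25% loss, m = 115 × 0.75 = 86.25: Φ(3.283 − 1.96) = 90.7% (t-test 90.4%).
- Loss at which 80% is just kept: 64 analysed per group gives 80.1% by t-test, and 1 − 64/115 = 44.3%.

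As a cross-check, 90% power needs 85 per group, and 85/0.75 = 113.3, so 114. The chosen 115 is almost exactly the size for 90% power at 25% attrition.

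**5. The reading under which the square is right.** Suppose 25% lose the effect but are all measured. The difference becomes 3.3 × 0.75 = 2.475, and n = 15.70 × (6.6/2.475)² = 111.6, so 112 per group.

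- 115 per group, 25% dilution, no loss: Φ(0.375 × √57.5 − 1.96) = Φ(0.884) = 81.2% (t-test 80.8%).
- 115 per group, 25% dilution and 25% loss: Φ(0.375 × √43.125 − 1.96) = Φ(0.503) = 69.2%.

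**The case against.** The best defence is that dilution was intended. The squared divisor is a recognised correction under intention-to-treat, and dilution is plausible in this trial. In the pilot, 63% completed all eight sessions, and women in both arms may receive other care. Read that way, 112 is correct and 115 per group gives about 81% power. This stands as a possible origin of the formula, and it is why the fix should offer two routes. It does not rescue the text, which mentions no non-adherence, cross-over or dilution and bases the 25% on loss to follow-up alone. If dilution was meant, loss to follow-up has no allowance at all.

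A second defence is that the G*Power paragraph already tells readers that 230 exceeds 80% power for a moderate effect. That is partly true, but the check takes n = 230 as given. The power at the plan's own 25% attrition is not stated.

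Three stronger readings are tempting and are not supported.

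- A reader might infer that the trial is underpowered. Under its stated assumptions the error runs the other way, and the article's conclusion that it can detect 3.3 points stands.
- A reader might infer that recruitment should stop at 168 to 172. Those totals hold only if loss is 25% and no dilution occurs. The article describes no stopping or extension decision that turns on this formula; it attributes the longer time frames to COVID-19 restrictions and reorganisation at recruiting sites.
- A reader might back-calculate heavy pilot attrition from pairs such as "negative affectivity (d = 0.84, p = .03) and stress reactivity (d = 1.08, p = .007", which would imply about 30 of 54 children analysed. That assumes plain two-group tests, which the article does not state, and uses rounded values at 9 months rather than 24. The maternal depression pair (d = 0.67, p = .05) implies about 37 of 54. Loss as high as 44% would in any case support 230 rather than undermine it.

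**Conclusion.** The point holds in a limited form. The inflation step does not match the reason given for it: for 25% loss to follow-up, 63 per group becomes 84 (86 by t-test), not 112. The target of 115 per group gives about 90% power at 25% attrition, and at least 80% up to about 44%.

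These figures rest on the plan's SD of 6.6, its difference of 3.3 points, a two-sided 0.05 test, equal loss in the two arms, and no dilution of the effect. The error is conservative and changes neither the analysis nor the type I error. It should be corrected because a published sample-size derivation does not yield its stated result for its stated purpose, but it does not threaten the validity of the trial.

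**What to change.** Keep 115 per group and amend the sample-size paragraph in one of two ways.

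1. If the 25% is loss to follow-up only, change the divisor to (1 − 0.25) and give 84 per group (86 with the t-test) as the number that meets 80% power. Then state that the chosen 115 per group provides about 90% power at 25% attrition and at least 80% up to about 44%.
2. If the square was meant for non-adherence or cross-over, say so, give the basis for 25%, and add a separate allowance for loss to follow-up. Report that 115 per group gives about 81% power with 25% dilution and complete outcomes, and about 69% with 25% dilution and 25% loss.

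In either case, say that the G*Power figures assume all 230 women are analysed, or recompute them after attrition. The cost is a few sentences of wording, with no extra participants and no change to design or analysis.

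### The stated 70% power for small effects at n = 230 does not reproduce at two-tailed 0.05 for any conventional small effect (33% to 57%, or 26% to 45% after the planned attrition)

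*Protocol article*

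**What the plan says.** All of this is in the protocol article, under Power & Sample size calculations, unless noted.

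- The size is derived "with 80% power at alpha (two-tailed) = 0.05". The pilot figure is that "the control group standard deviation (SD) for the Internalising scale was 6.6", and a "mean difference of 3.3 points is considered the MCID as it equates to ½ SD difference". The design effect is therefore d = 0.5.
- For loss to follow-up, "we are allowing for a prudent margin of 25% attrition", giving "112 which rounds to 115 per group (n = 230 in total"). Study design confirms two equal arms, "with a 1:1 allocation ratio to either CBT or TAU (n = 115 in each condition").
- A G*Power sensitivity analysis at n = 230 is then said to show that "both moderate and large effects have high reliability of being detected (power > 90"%) and that "small effects will be reliably detected with power = 70%; even in models including up to six covariates".

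For this last step the article gives no numerical value for small, moderate or large, no covariate R2 and no separate sidedness. Statistical analyses names a two-sample t-test, extended to ANCOVA, for the primary outcome.

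**The concern.** A trial sized for d = 0.5 with 80% power after 25% loss cannot usually also have 70% power for a small effect. The required sample size grows with the inverse square of the effect, so moving from 0.5 to 0.2 multiplies it by (0.5/0.2)^2 = 6.25. The claimed 70% therefore looked too high on its face.

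The calculation also uses all 230 women, although the preceding paragraph plans for a quarter of them to be lost.

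At stake is how a null result is read. A reader who accepts the sentence could take a non-significant difference, on the primary outcome or on the Externalising, cognitive or motor outcomes, as fair evidence against a small effect.

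**Working it through.** **Inputs from the article.** Two-tailed alpha 0.05; SD 6.6; difference 3.3 (d = 3.3/6.6 = 0.5); 115 per group; 25% attrition, so 115 × 0.75 = 86.25, taken as 86 per group; up to six covariates.

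**Assumption.** The size of a small effect, because the article does not give it. I use three values:
- d = 0.2, the usual convention (f = 0.10).
- d = 0.26, the lower of two effects that the Background (section on the CBT intervention) jointly labels small to medium.
- f2 = 0.02, the usual small value for a regression coefficient. With two equal groups f2 = d²/4, so d = 2√0.02 = 0.283.

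**Step 1: the figures that do reproduce.** n per group = 15.7 × (6.6/3.3)² = 62.8, so 63. Inflation: 63/(1 − 0.25)² = 63/0.5625 = 112, taken up to 115.

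**Step 2: power.** For n per group and k covariates, the noncentrality is δ = d√(n/2), with 2n − 2 − k degrees of freedom, and power = P(|T| > t at 0.975), with T noncentral t.
- n = 115: √57.5 = 7.583, critical value 1.970.
- n = 86: √43 = 6.557, critical value 1.974.

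| Effect | δ (115) | Power, 115 per group | δ (86) | Power, 86 per group |
|---|---|---|---|---|
| d = 0.20 | 1.517 | 32.7% | 1.311 | 25.6% |
| d = 0.26 | 1.972 | 50.1% | 1.705 | 39.6% |
| f2 = 0.02 (d = 0.283) | 2.145 | 57.0% | 1.855 | 45.4% |
| d = 0.50 | 3.791 | 96.5% | 3.279 | 90.3% |
| d = 0.80 | 6.066 | >99.9% | 5.246 | 99.9% |

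A normal approximation agrees. For d = 0.2 at 115 per group, Φ(1.517 − 1.960) = Φ(−0.443) = 32.9%. Removing six degrees of freedom for covariates changes no entry by more than about 0.02 percentage points. The claim for moderate and large effects holds; only the one for small effects fails.

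**Step 3: what 70% would require, two-sided.**
- At 115 per group: d = 0.33.
- At 86 per group: d = 0.38.
- For d = 0.2: about 310 analysed per group.
- For d = 0.2 at n = 230 with six covariates: covariates explaining about 63% of the outcome variance. The article states no such R2, and Table 1 schedules the CBCL only at 24 months, so there is no baseline value of the outcome to adjust for.

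**Step 4: possible sources of the 70%.**
- One-tailed test of a single coefficient, f2 = 0.02, N = 230: 68.9%.
- One-tailed, d = 0.2, with 230 in each group: 69.0%.
- One-tailed, d = 0.2, 115 per group: 44.7%.
- Omnibus F test, f2 = 0.02, six or seven predictors: 28% to 30%.

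The first two come close. The first conflicts with the two-tailed alpha, and the second also doubles the sample. Neither can be shown to be what was run.

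**The case against.** The best defence is that the article never says what small means. A sensitivity analysis can fix n and power and solve for the effect. At n = 230, two-sided 0.05 and 70% power, that gives d = 0.33, with or without six covariates. If small meant anything below 0.5, the 70% would be correct with no one-tailed test. This cannot be excluded as the route taken. It does not rescue the sentence: 0.33 is not a conventional small effect, it lies above the 0.26 that marks the small end of the article's own small-to-medium label, and at 86 per group its power is only about 58%.

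The absence of a definition does limit the charge. A reader might infer that power is overstated by more than a factor of two. That holds only at d = 0.2 (33% against 70%). At f2 = 0.02 the gap is 13 points before attrition, and the article does not say which value was used.

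The sentence also says openly that it uses n = 230, so the denominator is disclosed, and multiple imputation is planned. Imputation does not restore the full sample's power, however, so the figure still describes a data set the plan does not expect to have.

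Finally, effect sizes with confidence intervals are already planned, and these show directly whether a small effect is excluded. That stands and reduces the practical harm.

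**Conclusion.** Wrong as written, of moderate severity. At two-tailed 0.05 no conventional small effect has 70% power with 230 women: the range is 33% to 57% for d from 0.2 to about 0.28, and 26% to 45% with the planned attrition. This rests on the assumed range for a small effect and on the two-tailed alpha stated for the sample size also applying to the G*Power step. The one-tailed f2 = 0.02 calculation is a possible source of the figure, but unproven.

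A reader might go further and infer that the trial is underpowered or the sample size miscalculated. The article does not support that. The size rests on d = 0.5, its derivation reproduces, and power for that effect is 90.3% at 86 per group. No sample size, test or decision rule depends on the 70%.

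**What to change.** Replace the statement on small effects, and the n = 230 basis it shares with moderate and large effects, with:

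> With 25% attrition (86 analysed per group, two-sided alpha 0.05) power is 90% for d = 0.5, 80% for d = 0.43, 70% for d = 0.38 and 26% for d = 0.2; the trial is not powered for small effects.

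In the trial report, read non-significant results on the primary and secondary outcomes from the confidence intervals already planned under Statistical analyses, not from a design-stage power figure. If the authors hold the G*Power output and wish to keep a figure for n = 230, they should state the effect size, metric and sidedness behind it.

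The cost is wording only. Sample size, design and analysis stay as they are; a published figure becomes less favourable.
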